### Sample Size Considerations

The primary outcome measure-WOMAC physical function subscale- has been used to estimate the sample size required. The minimum clinically important difference (MCID) has been ascertained [66]. Using an MCID of 5.4 (SD = 11) on WOMAC Likert scale, with a significance level of 0.05 (2 tailed) and a power of 80%, it is estimated that 67 patients are required per group. To allow for 10% attrition at the 9 week follow-up, it is estimated that 74 patients will be required per group. However, as the waiting list control group will be re-randomised into 2 treatment groups after the 9 week follow-up, 50 patients per group will be required to give a total sample size of 150 patients.

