### Statistical Analyses

These will be blinded and will be performed in consultation with a statistician. Baseline and demographic data will be presented using descriptive statistics. Differences from baseline will be calculated for all primary and secondary outcomes. Mean differences, standard deviations and 95% confidence intervals will be calculated for all continuous outcomes. A longitudinal repeated measures design will be used to assess change from baseline and to make between group comparisons for the continuous outcome measures. Comparisons will be made between the 3 groups at the 9 week period. Participants in the control group will be analysed according to the intervention received after the 9 week follow-up and comparisons will be made between the 2 intervention groups at 18 weeks (both with and without the re-randomised control group subjects at the 18 week period). This will be done on an 'intention to treat' basis. Participants will be analysed in the intervention groups to which they were originally assigned and will include withdrawels and patients not treated by the assigned intervention. Missing data will be replaced using the last observation carried forward. Per-protocol analyses will also be performed by excluding patients with deviations from the treatment protocol.

At the 9 week and 18 week time points, continuous variables will be analysed using a mixed ANOVA model (with treatment as the between group factor and time as the repeated factor), or the non-parametric equivalent if non-normal distributions apply. Where significant differences occur, post-hoc comparisons will be conducted using Tukey's multiple comparison procedure. Differences in nominal/ordinal data will be analysed using the χ^2 ^test. A significance level of 0.05 will be set for any inferential statistics conducted.

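### The analysis of the primary outcome does not adjust for baseline WOMAC function; adjusting the 9-week score for it would gain precision at no cost, by an amount that depends on a correlation the protocol does not give

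*Protocol article*

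**What the plan says.** Under Statistical Analyses, the protocol article says "Differences from baseline will be calculated for all primary and secondary outcomes", and that a longitudinal repeated measures design will assess change and compare the groups. The three groups are compared at 9 weeks. At 9 and 18 weeks, "continuous variables will be analysed using a mixed ANOVA model (with treatment as the between group factor and time as the repeated factor"). The section also allows a fallback to another method: "or the non-parametric equivalent if non-normal distributions apply". Significant differences lead to Tukey comparisons. No baseline covariate is named, and the text does not say which term of the model carries the test of treatment.

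Under Sample Size Considerations, the inputs are given as "Using an MCID of 5.4 (SD = 11) on WOMAC Likert scale", two-sided 0.05 and 80% power, from which "it is estimated that 67 patients are required per group". After attrition the requirement is 74 per group, but the design settles on this: "50 patients per group will be required to give a total sample size of 150 patients". The section does not say whether 11 is the SD of the score or of the change. No baseline to follow-up correlation is given.

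**The concern.** Baseline WOMAC function is measured on every participant before randomisation, yet in the stated model it enters only as a level of the time factor or by subtraction. Both routes fix its weight at 1. A regression on baseline estimates the weight from the data and leaves less residual variation.

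This matters because the three-arm comparison at 9 weeks rests on 50 per arm, against the 67 per group that the protocol calculates before attrition. A gain in precision that needs no extra participants is worth having there. It would also settle which contrast is being tested, which the model description leaves open.

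**Working it through.** **Inputs.** From Sample Size Considerations: difference 5.4, SD 11, two-sided 0.05, 80% power, 67 per group, 50 per arm randomised, 10% attrition at 9 weeks. That leaves 50 × 0.9 = 45 per arm with 9-week data. Assumed, because the protocol does not give it: r, the correlation between baseline and 9-week scores, shown from 0.3 to 0.9. Also assumed: equal variance s² at the two visits.

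**The plan's own figure.** The normal approximation gives n = 2(1.96 + 0.84)² × (11/5.4)² = 65.1, so 66. The t-based calculation gives 67, since power is 79.9% at 66 and 80.5% at 67. The protocol's 67 is reproduced.

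**Equivalence.** With two visits, the treatment-by-time term is the difference between arms in mean (week 9 minus baseline). It is therefore a change-score comparison.

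**Variance per participant.**
- Change score: 2(1-r)s²
- Baseline-adjusted 9-week score: (1-r²)s²
- Ratio, adjusted to change: (1-r²) / [2(1-r)] = (1+r)/2, so the saving is 1 - (1+r)/2 = (1-r)/2

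| r (assumed) | Variance saving | Fall in standard error, 1 - √((1+r)/2) |
|---|---|---|
| 0.3 | 35% | 19% |
| 0.5 | 25% | 13% |
| 0.7 | 15% | 8% |
| 0.9 | 5% | 3% |

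A simulation (20,000 runs, 45 per arm) gave variance ratios of 0.76 at r = 0.5 and 0.86 at r = 0.7, against 0.75 and 0.85 from the formula.

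**Power for one pairwise comparison** (45 per arm, 5.4 points, t-test at two-sided 0.05, before any Tukey adjustment, which would lower every figure).

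*If 11 is the SD of change*, the adjusted residual SD is 11√((1+r)/2):
- r = 0.5: 9.53; power 63% unadjusted, 76% adjusted
- r = 0.7: 10.14; power 63% unadjusted, 70% adjusted

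*If 11 is the SD of the score*, the change SD is 11√(2(1-r)) and the adjusted SD is 11√(1-r²):
- r = 0.5: 11.00 and 9.53; power 63% unadjusted, 76% adjusted
- r = 0.7: 8.52 and 7.86; power 84% unadjusted, 90% adjusted

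**Which term is tested.** If raw scores are analysed with baseline and week 9 as the two time levels, the treatment main effect averages the two visits: (0 + 5.4)/2 = 2.7. The interaction recovers the full 5.4. In the simulation with score SD 11, the main effect averaged 2.73 (r = 0.5) and 2.69 (r = 0.7), with power 27% and 24%. The interaction averaged 5.43 and 5.40, with power 64% and 85%.

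**The case against.** The strongest reply is that the planned analysis is not wrong. Under randomisation a change-score comparison is unbiased, the article is condensed, and covariates are often settled in an analysis plan that is not shown. The first part stands: this is a matter of efficiency, not of validity. The last part does not dispose of the point, because the article does fix a model for continuous outcomes and that model has no baseline covariate.

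Four stronger readings are tempting, and the document does not support them.

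- *That a fixed share of precision, such as 15–25%, is lost.* That range is the variance saving for r between 0.7 and 0.5 only, and the protocol states no r. On the standard-error scale it is 8–13%.
- *That the plan will halve the treatment effect.* This needs raw scores with baseline as a time level and a reading of the main effect. Nothing says that the main effect will be read, and the stated purpose of assessing change from baseline points to the interaction. If changes are analysed, nothing is halved. With 18 weeks as a third level the dilution also differs: 3.6 if the effect is sustained, 1.8 if it has gone by then.
- *That chance baseline imbalance is left uncorrected.* A change score subtracts baseline with weight 1. With equal variances and r below 1, that over-corrects.
- *That the non-parametric fallback cannot address the question.* A rank test on change scores does compare change between arms at two visits, and the section separately promises mean differences with 95% confidence intervals.

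The power figures also depend on what the SD of 11 describes. If it is the SD of the score and r is 0.7, the unadjusted analysis already has 84% power for a single comparison and the gain is about 6 points. Finally, 45 is the number with observed 9-week data. The planned carry-forward of missing values would keep all 50 in the analysis.

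**Conclusion.** The point holds as a free improvement. The stated model uses baseline less efficiently than it could. The variance saving from adjustment is (1-r)/2, which is positive for any r below 1 under equal variances, and runs from 35% to 5% for assumed r of 0.3 to 0.9. For r of 0.5 to 0.7 the gain in power with 45 per arm is about 5 to 13 percentage points, depending on r and on the unstated meaning of the SD. The planned analysis remains valid and unbiased. The unnamed test term is a gap in wording to close, not evidence that the wrong term will be used.

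**What to change.** State as the primary analysis the 9-week WOMAC physical function score in a linear model with arm and baseline WOMAC function. Report the three pairwise adjusted differences with 95% confidence intervals, keeping the planned Tukey adjustment. Use the same form for the other continuous outcomes that have a baseline value.

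If the mixed ANOVA is kept, state that the treatment-by-time contrast at 9 weeks is the test, and not the treatment main effect.

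It would also help to say whether the SD of 11 refers to the score or to the change, so that the expected gain can be judged.

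The cost is analysis wording only. Baseline is already collected on all participants, and neither the sample size nor the visit schedule changes.

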### Global Assessment of Change (GAC)

Patient global assessment is one of the core domains which was recommended by OMERACT for evaluation in phase III trials in OA [63]. GAC comprises a single question which asks participants about the degree of change since their previous assessment and is therefore retrospective or transitional in nature. It functions as an external criterion to differentiate between changed and unchanged patients at the end of the study. It is subject to recall bias and can be heavily influenced by current status and patient satisfaction [67]. A 7-point Likert scale will be used ranging from 'very much worse' to 'very much better', with 'no change' located in the middle. The minimal clinically important difference of an average change of 0.5 on a 7-point scale has been found [68,69]. This will be measured at 9 and 18 weeks (and 27 weeks for the control group).

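### Ordinal outcomes, including by inference the 7-point Global Assessment of Change, go to an unordered chi-squared test that costs power, and the previous-visit anchor makes the week-18 rating ambiguous

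*Protocol article*

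**What the plan says.** The Statistical Analyses section of the protocol article has one sentence for categorical outcomes: "Differences in nominal/ordinal data will be analysed using the" χ² test. It names no trend or ordinal variant. The non-parametric alternative in the same paragraph applies only to continuous variables that are not normally distributed. The section adds: "A significance level of 0.05 will be set for any inferential statistics conducted".

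The GAC section describes the scale: "A 7-point Likert scale will be used ranging from" very much worse to very much better, with no change in the middle. It gives an important difference on the mean scale: "The minimal clinically important difference of an average change of 0.5 on a 7-point scale has been found". On the question itself it says: "GAC comprises a single question which asks participants about the degree of change since their previous assessment". On its purpose it says: "It functions as an external criterion to differentiate between changed and unchanged patients at the end of the study". The rating is taken at weeks 9 and 18, and at week 27 for the control group. There is no baseline value.

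At week 9 the plan compares three groups. At week 18 it compares the two interventions, both with and without the re-randomised controls.

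**The concern.** There are two separate points.

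**The test.** Pearson's chi-squared gives the same answer if the seven GAC categories are shuffled. It spreads its sensitivity over every possible departure, although the alternative of interest is a shift towards better. It estimates nothing, so it cannot be set against the 0.5-point important difference that the protocol quotes. Patient global assessment is, by the protocol's own account, a core domain for osteoarthritis trials, so the cost is worth measuring.

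**The anchor.** A question about change since the previous visit covers different intervals at different visits and in different cohorts. At week 18 an original-arm patient who improved by week 9 and kept the gain should choose the middle category. So should a patient who never improved. That conflicts with the stated role of separating changed from unchanged patients at the end of the study.

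**Working it through.** **The plan's own figure.** The protocol states no power or sample size for the GAC. Its only calculation is for WOMAC physical function: "Using an MCID of 5.4 (SD = 11) on WOMAC Likert scale", two-sided 5%, 80% power. The normal formula gives 2 × (1.96 + 0.84)² × (11/5.4)² ≈ 65.1, so 66. The t-test version gives 66.1, so 67, as stated. Then 67 × 1.1 = 73.7, so 74, as stated. These figures say nothing about the GAC, but 5.4/11 = 0.49 is a useful benchmark effect.

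**Group sizes.** Week 9: 50 × 0.9 = 45 per arm. Week 18 with re-randomised controls: 50 + 50/2 = 75 per arm, and 75 × 0.9 = 67.5, taken as 67. The protocol states 10% attrition for week 9; using it at week 18 is an assumption.

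**Degrees of freedom, all seven categories kept.** Two groups: (2 − 1)(7 − 1) = 6. Three groups: (3 − 1)(7 − 1) = 12. A rank test uses 1 and 2.

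**Analytic check.** Hold the noncentrality fixed and change only the degrees of freedom. Where the rank test has 80% power, the power falls to 52% (1 to 6 df) or 49% (2 to 12 df). Where it has 60%, it falls to 33% or 31%.

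**Simulation.** Assumed control distribution 3/7/15/40/20/11/4%, proportional-odds shift, two groups, two-sided 5%. Repeated runs agree to within about two percentage points.

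| Per group | Odds ratio | Chi-squared, 7 categories | Chi-squared, 3 categories | Rank test | Relative loss, 7 categories |
|---|---|---|---|---|---|
| 45 | 2.5 | 34% | 52% | 66% | 1 − 34/66 = 48% |
| 45 | 3 | 50% | 68% | 81% | 1 − 50/81 = 38% |
| 45 | 4 | 74% | 87% | 95% | 1 − 74/95 = 22% |
| 67 | 2.5 | 53% | 72% | 83% | 1 − 53/83 = 36% |

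For three groups of 45 at an odds ratio of 2.5, the figures are 35% against 69%. Under the null both tests reject at or near 5%.

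**The protocol's 0.5-point difference.** This needs an SD, which the protocol does not give. With rounded normal data and 45 per group, chi-squared against rank test gives 31% v 60% (SD 1.0), 22% v 46% (SD 1.2) and 14% v 33% (SD 1.5). With 67 per group it gives 50% v 78%, 32% v 62% and 22% v 46%. A shift of 0.49 SD gives 30% v 60% at 45 per group and 47% v 77% at 67.

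**Sparse cells.** Under the null, 45 × the assumed percentages gives expected counts of 1.35, 3.15, 6.75, 18, 9, 4.95 and 1.8. Four of the seven are below 5.

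**The anchor.** Setting the GAC wording beside the visit schedule:

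| Cohort | Week-9 rating covers | Week-18 rating covers |
|---|---|---|
| Original arms | treatment (from baseline) | after treatment (from week 9) |
| Re-randomised controls | waiting (from baseline) | treatment (from week 9) |

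In the pooled week-18 analysis about 50 of 75 per arm rate a post-treatment interval and about 25 of 75 rate a treatment interval. Controls are re-randomised between both interventions, so the mix should be similar in each arm. The comparison is therefore not biased under the null, but its result has no single meaning.

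**The case against.** The strongest reply is that a 7-category table is an inference. The chi-squared sentence does not name the GAC or say that all categories enter. The predictor analysis uses the GAC as a response in logistic regression, which suggests grouping there, and the earlier manual-therapy trial is summarised as percentages improved. Sparse cells would normally prompt collapsing, and that detail may sit in a document not shown. This stands as a limit on the size of the loss. It does not remove the point: the sentence assigns ordinal data to an unordered test, and collapsing still gives up power (52% against 66% at an odds ratio of 2.5).

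A reader might infer that the plan halves the power for the GAC and is likely to miss a real effect at week 9. The documents do not support that as a general statement. A loss of about half needs all seven categories, about 45 per arm and a modest effect. The earlier trial's 81% against 50% is an odds ratio of (0.81/0.19)/(0.50/0.50) = 4.3. A chi-squared test on improved yes/no would detect that contrast with about 89% power at 45 per arm, though nothing says this trial's effects will be that large.

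A reader might also infer that the GAC cannot show sustained change at all. That is too strong. At week 9 the previous assessment is baseline, so the three-group comparison is sound. For re-randomised controls the week-18 rating covers their treatment. The original arms' week-9 rating is also collected and can be read with week 18, although no joint reading is described. WOMAC, pain and the physical tests measure maintained benefit directly. The plan also has a week-18 analysis without the re-randomised controls, which avoids the mixing.

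**Conclusion.** The point holds as a matter of efficiency and interpretation on a secondary outcome. It does not concern bias, type I error or the primary analysis.

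The plan gives ordinal outcomes a test that discards their order and yields no estimate. For two groups of 45 with seven categories kept, the relative loss against a rank test is about 48% at an odds ratio of 2.5 and 22% at 4. With 67 per group it is about 36% at 2.5. With three categories and 45 per group it is 1 − 52/66 = 21% at 2.5. All of these rest on an assumed category distribution, because the protocol gives none.

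The anchor is sound at week 9. At week 18 the original arms' rating, taken alone, cannot tell maintained from absent improvement, and the pooled comparison combines two reference intervals.

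**What to change.** **Test.** Limit the chi-squared sentence to nominal data. Analyse ordinal outcomes with a Kruskal-Wallis or Mann-Whitney test, or with a proportional-odds model reporting a common odds ratio and 95% confidence interval. The cost is one sentence, plus a check of the proportional-odds assumption if the model is used. Sample size and visits do not change.

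**Anchor.** In the pooled comparison, take each participant's GAC from the assessment at the end of their own treatment period: week 9 for the original arms, week 18 for re-randomised controls. Every rating then covers a treatment interval, and no questionnaire change is needed. Interpret the original arms' week-18 rating jointly with their week-9 rating, and say so in the plan.

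Re-anchoring the later question to the start of treatment is an option, not a requirement. It would measure sustained change directly, but it lengthens recall from about 9 to about 18 weeks for the original arms at week 18, on an item that the protocol already describes as prone to recall bias.

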### Predictors of response to treatment

Treatment effectiveness can be improved by matching treatment to patient characteristics to determine what works best for whom. Few studies have evaluated predictors of response to physiotherapy in hip OA. Hoeksma et al [49] found that patients with mild/moderate radiographic changes who received manual therapy had significantly better range of motion outcomes than those with severe changes. Manual therapy had no differential effect on subgroups of patients defined by baseline pain or hip function. This secondary analysis did not evaluate the outcome of the exercise intervention on different subgroups. Female gender, low co-morbidity, absence of depressive symptoms and a history of receiving complementary medicine in the previous 12 months were the most stable predictors of outcome in a non-randomised study of inpatient rehabilitation for hip or knee OA [50]. In this proposed study, patients of varying severity will be included and it is possible that treatment effects may be different in groups of patients with different characteristics, such as x-ray severity and symptomatic severity.

In summary, a multi-centre randomised controlled trial that compares the clinical effectiveness of a combination of manual therapy and exercise therapy, exercise therapy only and a waiting-list control will be conducted. This study also will examine if any clinical baseline features predict response to treatment as a secondary analysis.

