## Methods

### Aim

The primary aim of this study is to compare the effect of a combination of manual therapy and exercise therapy, exercise therapy only and a waiting-list control on physical function in hip OA.

A secondary aim of the study will be to investigate the effect of baseline variables such as age, gender, body mass index, disease severity, baseline pain, physical function, mood and co-morbidities on treatment outcome.

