### WOMAC (Western Ontario and McMaster Universities) Osteoarthritis Index Physical Function Subscale

The WOMAC is a multidimensional, self-administered health status instrument. It is available on both a 5-point Likert scale and a 100 mm visual analogue scale (VAS). In this study, the Likert version will be used. WOMAC consists of 24 questions regarding pain (scored 0–20), stiffness (scored 0–8) and physical function (scored 0–68). It has been shown to be a reliable, valid and responsive multidimensional outcome measure in patients with osteoarthritis of the hip or knee [64] and has been found to demonstrate superior responsiveness to the Lequesne Algofunctional Index [65]. Minimal perceptible clinical improvement has been found to be 9.3 mm on the physical function subscale on the WOMAC 100 mm normalised VAS [66].

Secondary Outcome Measures include:

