Secondary analysis will be undertaken to assess the predictors of outcome at primary endpoint (9 weeks post treatment) in both intervention groups, using multiple regression analyses. A number of predictor variables such as age, gender, x-ray severity, baseline pain, physical function, mood, co-morbidities and treatment expectations will be measured. Analyses will be performed separately for exercise therapy, and combined exercise and manual therapy. Response variables will be change in WOMAC physical function score pre and post intervention (MCID> 5.4) and Global Assessment of Change. All predictors will be checked for collinearity. Univariate logistic regression will be performed on all potential predictors and those associated with the outcomes will be entered into the multivariate logistic regression model and backward regression will be performed. Variables with the lowest predictive value will be removed from the model if p > 0.05. Odds ratios and 95% confidence intervals will be calculated for all final predictors.

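### Baseline function is tested as a predictor of a WOMAC response that is itself calculated from baseline, so the 0.05 test for that predictor is not valid

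*Protocol article*

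**What the plan says.** The secondary aim (Aim) is to study the effect of "baseline variables such as age, gender, body mass index, disease severity, baseline pain, physical function, mood and co-morbidities on treatment outcome". The last paragraph of Statistical Analyses sets out how:

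- **Responses:** "Response variables will be change in WOMAC physical function score pre and post intervention (MCID> 5.4) and Global Assessment of Change". The models are logistic, so the WOMAC response is a yes/no variable cut at 5.4 points.
- **Candidate predictors:** "A number of predictor variables such as age, gender, x-ray severity, baseline pain, physical function, mood, co-morbidities and treatment expectations will be measured".
- **Selection:** "Univariate logistic regression will be performed on all potential predictors and those associated with the outcomes will be entered into the multivariate logistic regression model", followed by backward elimination: "Variables with the lowest predictive value will be removed from the model if p > 0.05". Odds ratios with confidence intervals are reported for the predictors that remain.
- **Analysis set:** each therapy group is modelled alone. The waiting-list group is not used as a reference.

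The WOMAC section gives the function subscale a range of 0 to 68. Table 1 sets no minimum function score, and the Background says that "patients of varying severity will be included". The one safeguard stated is a check for collinearity. That check compares predictors with each other, not a predictor with the response.

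**The concern.** Improvement is baseline minus week 9, so the baseline score appears on both sides of the model. A patient who scores unusually badly at baseline, partly through day-to-day variation or measurement error, will tend to score closer to the average at week 9 and so show a larger fall. This happens even if treatment helps everyone by the same amount. The null hypothesis of no association between baseline and response is then false for reasons unrelated to treatment, and a 0.05 test of it does not test whether benefit depends on baseline function.

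The floor adds a little. Scores are whole numbers, so a fall of more than 5.4 means at least 6 points, and a patient starting at 0 to 5 cannot be a responder.

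At stake is one part of the secondary aim. The Discussion hopes that predictors will help tailor rehabilitation. An odds ratio suggesting that more disabled patients respond better could be read in that light although much or all of it came from how response was defined. Because each therapy group is modelled alone, no comparison with untreated patients would expose this.

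**Working it through.** The article gives no figure for the predictor analysis, so there is none of its own to reproduce here.

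**Inputs from the article.** Response cut 5.4; SD 11; 50 patients per group; 10% attrition, hence 50 × 0.90 = 45 (Sample Size Considerations). Scale 0 to 68 (WOMAC section). Test level 0.05 (Statistical Analyses).

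**Assumptions not in the article.** Baseline mean 32; the same true benefit of 5.4 points for every patient; SD 11 read as the SD of the score; baseline to week-9 correlation r from 0.5 to 0.9; week-9 SD equal to k times the baseline SD, with k = 1 first and then larger.

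**Step 1, built-in correlation.** With constant benefit,

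corr(baseline, improvement) = (1 − rk) / √(1 + k² − 2rk).

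For k = 1 this is √((1 − r)/2). At r = 0.5 it is √0.25 = 0.50; at r = 0.7, √0.15 = 0.39; at r = 0.8, √0.10 = 0.32; at r = 0.9, √0.05 = 0.22.

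**Step 2, chance of being a responder.** With k = 1 and a mean change equal to the cut, a patient j SDs from the baseline mean responds with probability Φ(j√((1 − r)/(1 + r))). At r = 0.5 the root is √(0.5/1.5) = 0.577, so the probability is 28%, 50% and 72% at −1 SD, the mean and +1 SD. At r = 0.9 it is 41%, 50% and 59%. True benefit is identical for all of these patients.

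**Step 3, how often baseline is declared a predictor.** Scores were simulated, rounded and kept within 0 to 68. Response (a fall of more than 5.4) was regressed on baseline function in a univariate logistic model and tested at 0.05 (Wald), with n = 45:

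| r | k = 1 | k = 1.1 |
|---|---|---|
| 0.5 | 79% | 62% |
| 0.6 | 67% | 47% |
| 0.7 | 53% | 32% |
| 0.8 | 39% | 16% |
| 0.9 | 22% | 5% |

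Repeat runs agree to within about two percentage points. The formula in Step 1 explains the second column: at k = 1.1 and r = 0.9 the built-in correlation is (1 − 0.99)/√(1 + 1.21 − 1.98) = 0.01/0.48 = 0.02, so almost nothing is left. With k = 1.2 the rates are about 48%, 31%, 15% and 5% at r = 0.5, 0.6, 0.7 and 0.8.

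**Step 4, check on the cause.** When change is generated independently of baseline, the rate returns to 4–6%. The coupling, not the logistic model or the sample size, produces the excess.

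**Step 5, larger groups.** If re-randomised controls are added, each group has about 50 + 25 = 75 patients, or about 67 after attrition. With k = 1 and n = 67, the rate is 93% at r = 0.5, 74% at 0.7, 56% at 0.8 and 31% at 0.9. More patients make the problem worse, as expected of a bias.

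**Step 6, the floor.** The share of patients with a baseline of 0 to 5 is about Φ((5.5 − 32)/11) = Φ(−2.41) = 0.8% with an assumed mean of 32, and Φ((5.5 − 25)/11) = Φ(−1.77) = 3.8% with a mean of 25. The floor is a minor contributor.

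**Step 7, an analysis without the problem.** The week-9 score was modelled on baseline, treatment (therapy against waiting list) and their interaction in the same setting, with 45 to 50 per group and r of 0.5, 0.7 and 0.8. The interaction was significant in 4.5–5.0% of runs, close to the nominal level.

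**The case against.** The coupling itself is not in dispute. The objections concern its size and reach, and several stand.

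- **Frequency.** A reader might infer that baseline function will usually be found to predict response. The article does not support that without conditions, because it gives neither the correlation nor the week-9 spread. With 45 per arm and equal spread, the rate is below one half at r = 0.8, and a modestly larger week-9 spread lowers it further. This stands.
- **Missing data.** The article replaces missing values by the last observation carried forward. If that rule covers this analysis, a dropout with no week-9 score has zero change and is a non-responder at any baseline. With 5 such patients among 50, the rates become about 73%, 48%, 37% and 19% at r = 0.5, 0.7, 0.8 and 0.9. This is a modest reduction, and the test remains invalid.
- **Instrument.** The predictor list says only physical function. SF-36 physical functioning and two performance tests are also measured, and these would be coupled only indirectly. WOMAC is the natural reading because it is the primary measure of function, but it remains a reading.
- **Second response.** Global Assessment of Change is not computed from the baseline score, so the artefact does not carry over to it.
- **Other predictors.** A reader might infer that the results for pain, mood or x-ray severity are spoiled as well. This was not shown. Where baseline function stays in the multivariable model, those predictors are already adjusted for it.
- **Consequences.** A reader might also infer that the trial would end up recommending treatment for the more disabled. The Discussion says only that such factors may help tailor rehabilitation.

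None of this restores a valid test for baseline function against the WOMAC response.

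**Conclusion.** The point holds in a limited form. Tested as written, baseline WOMAC function has a built-in association with the WOMAC response, in the direction of worse function predicting response, and nothing in the article deals with it. With equal spread at both visits, constant benefit and 45 per arm, the false-finding rate per arm runs from about 79% (r = 0.5) to 22% (r = 0.9), against a nominal 5%. With a week-9 SD 1.1 times the baseline SD it runs from 62% to 5%. The rate therefore exceeds 5% in most settings tried, but its size rests on two quantities the article does not supply.

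It would be too strong to say that the WOMAC response measures only regression to the mean and the floor: a genuine difference in benefit by baseline would contribute too, but a single-arm model cannot separate the two. The conclusion covers one predictor, one of two responses and a secondary analysis. The primary between-group comparison is not affected. The change is worth making because the analysis is fixed in the text and easily corrected.

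**What to change.** In the predictor paragraph of Statistical Analyses:

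1. For the WOMAC predictor models, use the week-9 physical function score as the response and always include baseline WOMAC function as a forced covariate. Judge the other predictors at equal baseline function.
2. State that the coefficient of baseline function is not evidence of response to treatment. If the responder model cut at 5.4 is kept as supportive, force baseline function into it and attach the same statement.
3. Name the instrument meant by physical function in the predictor list.
4. To keep the question about baseline function that the secondary aim asks, test a baseline-by-treatment interaction on the week-9 score, comparing the therapy groups with the randomised waiting-list group.

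This needs no new patients, visits or measurements. The cost is that the single-arm odds ratio for baseline function is no longer reported as a predictor, and that the interaction test has limited power with about 45 to 50 patients per group. It should be presented as exploratory, with its confidence interval.
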